### Assessment process

#### Screening for eligibility

Young people referred to CAMHS are provided with a routine assessment by an intake clinician. Potential participants who are deemed suitable for treatment at the service and meet study criteria are then invited to take part in the study. The assessing clinician obtains consent or assent from the youth and parent and collects the demographics data. Those who are eligible and have given consent are then randomized, and a study site coordinator allocates a clinician to provide therapy according to treatment group allocation.

#### Baseline measurement

Once the clinician has established with the youth and parent the key problems, using the Top Problems Assessment in a face-to-face session, weekly ratings on these are collected by the research assistant via telephone. Other baseline measures are collected by the research assistant.

#### Weekly measurements

The allocated research assistant completes the weekly telephone assessments with the parent and the youth participant for the duration of treatment. The weekly assessment is designed not to exceed 10 minutes, to minimize participant burden.

#### Monthly assessment

Once a month, in addition to the weekly measures, the research assistant conducts the Strengths and Difficulties Questionnaire (parent- and youth-rated) assessments.

#### Post-intervention assessment

The post-intervention assessment occurs once a clinician has discharged the youth from treatment and is conducted by the research assistant.

#### Three month follow-up

Three months after the post-intervention assessment, a final follow-up assessment is conducted by the research assistant.

Participant flow is outlined in Fig. 1. The study procedures are summarized in Table 1.

**Fig. 1 Fig1:**
[figure not shown]
Participant flow. Note that this is the original flow chart and has been amended to 100 participants per arm with the reduced recruitment target. As many participants as possible are recruited from Kaupapa Māori and Pacific services. CAMHS, Child and Adolescent Mental Health Services; EBT, evidence-based treatment; MATCH, Modular Approach to Therapy for Children with Anxiety, Depression, Trauma, or Conduct; RA, research assistant; UC, usual care

### Sample size

Overall, a sample size of 60 clinicians and 400 patients will provide sufficient power to detect effect sizes of approximately 0.37, well below the effect size shown by the comparable USA study [30]. The initial power calculation was to allow independent analysis to be undertaken for Māori and Pacific participants and ensured sufficient power (80 %) to detect moderate effect sizes of between 0.61 and 0.70 as statistically significant (two-tailed *α* = 0.05) in these groups (equivalent to the effect sizes found in the USA study [30]). This estimate allowed for a 15 % attrition rate in clinicians and in clients (based on the 12.3 % attrition rate reported in Weisz *et al.* [30] and adjustment for the clustering of patients with clinicians (intraclass coefficient = 0.1)). We assumed approximately six to eight patients per clinician (approximately 400 patients). If fewer clinicians were available within the targeted services, we planned to increase the number of participants per clinician to ensure that we maintained statistical power. The intention was to recruit approximately 12 clinicians working in Kaupapa Māori services and approximately 12 clinicians working in Pacific services. While this seemed feasible in the planning stages, when we were actually conducting the trial, there were a number of staffing difficulties in the services overall, and these impacted more particularly in the Kaupapa Māori and Pacific services, perhaps because of the smaller pool of people in the workforce. This led to difficulty in recruiting clinicians working in Māori and Pacific services, with resulting reduced ability to recruit participants to the trial from those services. It became evident that we would not reach the targets for Māori and Pacific participants to allow ethnic-specific analysis, as planned. An interim blinded-to-treatment allocation, single group, power analysis was undertaken (when approximately 50 participants had completed treatment) to determine the total number of participants needed to show overall clinical effectiveness for the whole sample. This summary produced a standard deviation for the change in the parent-rated Brief Problem Monitor of 4.4, which indicated that to show a clinically important difference in the change (>2 units) as statistically significant (two-tailed *α* = 0.05) with 80 % power, a total sample size of 160 participants would need to be recruited. A total sample of 200 participants would provide 90 % power for this comparison. Although a reduced final sample size would compromise the ethnic-specific analysis, it was felt that the primary question of whether MATCH-ADTC improved the trajectory of change of clinical severity more than usual care could be conclusively addressed with 200 participants. Based on the ongoing recruitment, it was anticipated that this total recruitment could be achieved if we extended the timeline and recruited until the end of June 2015.

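### The revised power figures (160 for 80 %, 200 for 90 %) match only a calculation without clustering or attrition; under the plan's own ICC of 0.1, 200 participants give about 76-82 %

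*Protocol article*

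**What the plan says.** All the figures are in the Sample size section of the protocol article.

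- **Original design.** 60 clinicians and 400 participants, with a detectable effect size of about 0.37. The calculation included a 15 % attrition rate for clinicians and clients and an "adjustment for the clustering of patients with clinicians" with an intraclass coefficient of 0.1.
- **Revised design.** A blinded, single-group look, taken when about 50 participants had completed treatment, gave "a standard deviation for the change in the parent-rated Brief Problem Monitor of 4.4". The aim is "to show a clinically important difference in the change (>2 units" or more, at "two-tailed *α* = 0.05) with 80 % power". From this the article concludes that "a total sample size of 160 participants would need to be recruited" and then that "A total sample of 200 participants would provide 90 % power for this comparison". It mentions neither clustering nor attrition here.
- **Conclusion drawn.** The primary question "could be conclusively addressed with 200 participants".

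Three other places bear on the point. The Design section says that clinicians are randomized to one arm, and that data from all participants are analysed even where assessments are incomplete. Withdrawal criteria provides for withdrawals and for follow-up of treatment dropouts where possible. Clinical outcomes, under Statistical methods, makes the primary analysis a mixed model of trajectories.

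**The concern.** One section uses two sets of rules. The original target carried allowances for clustering and attrition; the revised one appears to carry neither. Both features remain: clinicians still deliver one arm only and treat several youths each, and participants can still withdraw. The article also reports difficulty in recruiting clinicians, and says that with fewer of them it had planned more participants per clinician, which increases the clustering penalty.

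What is at stake is how the result is read. The smaller target is defended by the 90 % figure. If the chance of missing a true 2-unit difference is about 18-24 % rather than 10 %, a non-significant result says less about the absence of that benefit than the article implies.

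**Working it through.** **Inputs** (Sample size section): SD 4.4; difference 2; two-sided α 0.05; 15 % attrition; ICC 0.1; 60 clinicians. The 1:1 allocation is from the Design section. The 51 clinicians used below are 60 × 0.85. The article gives no revised clinician number, so 51-60 is an assumption.

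**Step 1: reproduce the stated figures without allowances.**

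Total N = 4 (z₁₋α/₂ + z_power)² (SD/difference)²

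- 80 %: 4 × (1.960 + 0.842)² × (4.4/2)² = 152
- 90 %: 4 × (1.960 + 1.282)² × (4.4/2)² = 203.4, so 204 in equal arms

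Power = Φ(2 / [4.4 √(4/N)] − 1.960)

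- N = 160: 82.0 %
- N = 200: 89.5 %

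The stated figures are reproduced to rounding. A 5 % loss allowance could explain 160 (152/0.95 = 160), but on the same basis 90 % would need about 215 (204/0.95). The figure of 200 leaves no room for either allowance.

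**Step 2: apply the plan's own allowances.**

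Design effect DE = 1 + (m − 1) × 0.1, with m = participants analysed per clinician. Effective N = analysed / DE, which then goes into the power formula above. The last column is (1.960 + 1.282) × 4.4 × √(4/effective N).

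| Recruited | Loss | Clinicians | m | DE | Effective N | Power for 2 units | Detectable at 90 % |
|---|---|---|---|---|---|---|---|
| 200 | 0 | 60 | 3.33 | 1.233 | 162.2 | 82 % | 2.24 |
| 200 | 0 | 51 | 3.92 | 1.292 | 154.8 | 81 % | 2.29 |
| 200 | 15 % (170) | 60 | 2.83 | 1.183 | 143.7 | 78 % | 2.38 |
| 200 | 15 % (170) | 51 | 3.33 | 1.233 | 137.8 | 76 % | 2.43 |
| 160 | 0 | 60 | 2.67 | 1.167 | 137.1 | 76 % | 2.44 |
| 160 | 0 | 51 | 3.14 | 1.214 | 131.8 | 74 % | 2.48 |
| 160 | 15 % (136) | 60 | 2.27 | 1.127 | 120.7 | 70 % | 2.60 |
| 160 | 15 % (136) | 51 | 2.67 | 1.167 | 116.6 | 69 % | 2.64 |

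Attrition alone, with no clustering, gives 84 % at 200 and 76 % at 160.

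**Step 3: sensitivity to the SD.** An SD of 4.4 from about 50 participants has a 95 % confidence interval of roughly 3.7 to 5.5. With both allowances and 60 clinicians, power at 200 is about 90 % at SD 3.7, 85 % at 4.0, 78 % at 4.4 and 67 % at 5.0. The uncertainty runs both ways.

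**Step 4: what the original 0.37 shows.** At 80 % power the detectable effect size is (1.960 + 0.842) √(4/effective N).

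- No allowance: 0.28
- 15 % attrition alone: 0.30
- ICC 0.1 alone, 8 per clinician (400/1.7 = 235): 0.365
- Both, 340 analysed over 60 clinicians (DE 1.467, effective N 232): 0.368
- Both, 340 over 51 clinicians (DE 1.567, effective N 217): 0.380

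So 0.37 is consistent with a clustering adjustment, with or without attrition. It is not consistent with no clustering.

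**The case against.** **The arithmetic is right on the inputs given.** This stands. The 160 and 200 follow from SD 4.4 and a 2-unit difference. The fault is in the assumptions. The article does not say that the allowances were dropped; that is inferred from which formula reproduces the figures.

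**Attrition need not mean lost participants.** This stands in large part. All participants enter the analysis, the model uses weekly ratings, and treatment dropouts are followed where possible. A reader might infer that the true power is simply 76-78 %. The documents do not support this as a fact, because it treats 15 % attrition as complete loss. It is the lower end of a range whose upper end, with clustering alone, is about 81-82 %.

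**The 0.37 does not prove both allowances.** This stands, as Step 4 shows. The case rests on the article's statement that both were used, not on back-calculation.

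**The planned model may be more efficient than a change score.** Baseline adjustment and weekly ratings could reduce error variance, so power for the slope cannot be derived from this document. But the article itself bases its 90 % on an SD of change and applies it to the trajectory question, so that efficiency is not yet part of the claim.

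**The pooled SD contains any treatment effect.** Removing a 2-unit difference gives an SD of about 4.28, and power at 200 with both allowances and 60 clinicians rises only to about 80 %.

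**There may be more than 60 clinicians.** The abstract says at least 60. With 80 clinicians and both allowances, power is about 80 %; with clustering alone it is about 85 %.

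**Conclusion.** The concern holds as a matter of sample-size assumptions. For 200 participants, the stated 90 % allows for neither of the two features that the same section had built into the original target. On the change-score basis that the article uses, with SD 4.4, a 2-unit difference, ICC 0.1, 51-60 clinicians and 0-15 % loss, power is about 76-82 % at 200 and about 69-76 % at 160. The difference detectable with 90 % power at 200 is about 2.2-2.4 units.

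The range depends on the ICC of 0.1 carrying over to the change score and on the clinician number, which the article does not update. At SD 4.4, either stated allowance taken alone already brings 200 below 90 % (attrition 84 %, clustering 81-82 %).

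A reader might go further and conclude that 200 participants are too few or that the trial cannot answer its question. The documents do not support that. Power near 80 % is plausible on these assumptions, a smaller SD would raise it, and a slope-based calculation might too. What they do not support is the stated 90 % or the word *conclusively*.

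**What to change.** Either of two changes to the Sample size section would do:

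1. **Restate the range.** Give about 76-82 % power for 200 participants and about 69-76 % for 160, for a 2-unit difference, conditional on SD 4.4, ICC 0.1, 0-15 % loss and 51-60 clinicians. Replace 51-60 with the actual number of clinicians treating participants. Delete *conclusively*. If uncertainty in the SD is mentioned, show it in both directions.
2. **Recompute for the planned analysis.** Estimate power for the slope difference in the mixed model from pooled blinded data, with the clinician ICC and expected attrition included, and state that figure with its assumptions in place of the 90 %.

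The first costs wording only, and the stated power becomes less favourable. The second costs a short blinded calculation. Neither changes the number enrolled or needs unblinding.

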
### Randomization and sequence generation

Youth are recruited over many months, and are not all available for randomization at the outset of the trial, whereas the clinicians had to be randomized initially so that those in the MATCH-ADTC condition could all receive training prior to recruiting youth for the study. We believe that any possible selection bias has been avoided, as any youth participant who is randomized can then be immediately allocated to their randomization group. Because this random allocation was carried out by the study team, with no input from clinicians or clinic staff, there was no possibility of the screening or allocation process being biased by any of the treating clinicians. The randomization sequences for clinicians and youth participants were electronically generated in permuted blocks prior to any recruitment and loaded into the eMonitor system.

### Allocation concealment

Allocation concealment for the participants and researchers has been assured by using centralized computer allocation of the randomization sequence. The randomization list is not available to any members of the research team directly involved in the assessment or screening of participants. A participant is only randomized once all entry criteria are met. After the details of a consenting participant are entered online, the eMonitor informs the study site coordinator or the clinician of the randomized group allocation.

### Blinding

Owing to the nature of the study, double blinding is not possible, as clinicians are aware of the treatment they are administering. We anticipate that despite signing informed consent, most youth and their parents will effectively be blind to treatment allocation. At entry to the study, the information conveyed to the participants (orally and in writing) has been designed to ensure that details that could easily distinguish MATCH-ADTC from usual care are not provided, but that accurate information is given. We explain that both treatments are thought to be effective and that the purpose of this research is to compare treatments to see if one is better than the other. All research assistants collecting telephone administered assessments and coding the therapy sessions are blind to treatment allocation throughout the study. Participants are asked not reveal the details of the intervention they are receiving to the research assistant. All participants are given an identification number to ensure that the researchers involved in data management and manipulation are unaware of the treatment allocation.

### Statistical methods

#### Interim analysis

When recruitment was lower than anticipated, a single interim blind calculation of the standard deviation of the change in the primary outcome parent-rated Brief Problem Monitor for all participants as a single group was undertaken, to determine the utility of recruiting a smaller sample size than originally planned. As this summary did not involve a comparison between randomized groups, no adjustment to the *α* level for protection of the type I error rate was required.

#### Overall analysis

The comparability of the baseline status of both treatment groups (i.e., MATCH-ADTC and usual care) will be determined using descriptive analysis, in terms of age, sex, clinical symptom severity, diagnosis, and ethnicity. The two randomized treatments may vary in duration, so that post-intervention and follow-up (three months after treatment has ended) analyses are potentially confounded by treatment duration. To allow an unconfounded interpretation, we propose to use the trajectories of change across time on the parent-rated Brief Problem Monitor as our primary outcome measure. The trajectory of change was selected in part because the duration of treatment and number of sessions provided to individual youth are variable in usual clinical services, and also within the structure of the MATCH-ADTC program, such that the usual care and MATCH-ADTC groups could not be matched for duration or number of sessions. In addition, we want to compare the results of the current study with that of a trial from the USA that used this method [30]. The primary analysis will be based on the intention-to-treat population, but sensitivity analysis will be undertaken on the per-protocol population.

#### Primary outcomes

##### Clinical outcomes

The difference in the trajectories between groups will be tested using a mixed effects regression model: *a*_0_ (intercept) + *a*_1_ (participant) + *a*_2_ (treatment group) + *a*_3_ (time) + *a*_4_ (treatment × time) and intercept and participant as random effects. These analyses will further include terms for:Service type (i.e., Kaupapa Māori, Pacific and ‘mainstream’ CAMHS);Clinicians’ previous training in evidence-based therapy;Baseline symptom level; andMedication use.

Although we are now unable to conduct ethnic-specific analysis, summary data will be used to illustrate whether there is a broad consistency of the clinical outcome results across ethnicity groups.

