## Methods

### Design

This study is a multi-site effectiveness randomized controlled trial comparing MATCH-ADTC with usual care [41]. Prior to randomization, written informed consent is obtained from each participant. Randomization is implemented on two levels: first, randomization of participating clinicians, then randomization of youth participants. For the randomization of clinicians, all clinicians from participating services were invited to participate and provide written informed consent. Consenting clinicians were block randomized (by service or team) in a 1:1 ratio to MATCH-ADTC or usual care. The block size varied across sites, depending on the number of individual clinicians recruited from each site. Clinicians were stratified on the basis of previous training in evidence-based therapies (i.e., those with versus those without training in cognitive behavioral therapy or behavioral parent training). Clinicians randomized to MATCH-ADTC received training in MATCH-ADTC at the beginning of the study prior to the recruitment of youth participants. Those randomized to usual care will receive training at the end of the study (once all follow-up data have been collected). Randomization of youth participants occurs after a clinician-administered eligibility check and once written consent has been obtained. Youth participants are then randomized in a 1:1 ratio to receive MATCH-ADTC or usual care, with participants stratified by sex and ethnicity (Māori, Pacific, or ‘other’). Web-based randomization procedures are used to determine treatment allocation. Data from all participants will be included in data analysis, irrespective of whether or not all assessments have been completed.

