### Withdrawal criteria

Participants (youth and their parents, or study clinicians) can withdraw from the study at any time. Those participants who remain in the study but have dropped out of treatment are followed up wherever possible. Where a clinician withdraws from the study, a clinician from the same treatment arm will continue to provide the treatment allocated (i.e., either MATCH-ADTC or usual care).

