##### Delivery of evidence-based treatments

The percentage of evidence-based content and quality of delivery of therapy in a 10 % random subset of sessions assessed by coding audio-taped therapy sessions will be compared between groups using an analysis of variance (ANOVA) model, following the method used in the trial in the USA study [30].

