##### Efficiency of service delivery

Efficiency in delivery of therapy for MATCH-ADTC and usual care will be compared using ANOVA to test for significant differences using the following data which will be collected from the clinical service, including:Clinician time (in minutes);Duration of contact with the service (in weeks);Number of therapy sessions; andNumber of missed therapy sessions.

If any of these outcomes do not meet the assumptions for parametric ANOVA models, the data will be transformed as appropriate prior to analysis.

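### The stated primary analyses carry no clinician effect, although clinicians are nested within arm and the original sample size assumes a clinician ICC of 0.1

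*Protocol article*

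**What the plan says.** **Design.** The protocol article (Design) randomises at two levels. For clinicians: "Consenting clinicians were block randomized (by service or team) in a 1:1 ratio to MATCH-ADTC or usual care". For youths: "Youth participants are then randomized in a 1:1 ratio to receive MATCH-ADTC or usual care". Only the MATCH-ADTC clinicians are trained before youths are recruited. Under Withdrawal criteria, if a clinician leaves, "a clinician from the same treatment arm will continue to provide the treatment allocated". So each clinician works in one arm and clinicians are nested within arm.

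**Sample size.** The original calculation (60 clinicians, 400 youths) includes "adjustment for the clustering of patients with clinicians", with an ICC of 0.1. The revised calculation (160 youths for 80 % power, 200 for 90 %) uses a standard deviation of change of 4.4 and a difference of 2, and mentions no clustering.

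**Analyses.**
- Clinical outcomes: "The difference in the trajectories between groups will be tested using a mixed effects regression model". The equation is written out. Intercept and participant are the random effects. Service type, clinicians' previous training, baseline symptom level and medication use are added. There is no clinician effect.
- Delivery of evidence-based treatments: a 10 % "random subset of sessions assessed by coding audio-taped therapy sessions will be compared between groups using an analysis of variance (ANOVA) model", said to follow the US trial's method.
- Efficiency of service delivery: clinician time and related measures "will be compared using ANOVA to test for significant differences".

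**The concern.** When each clinician delivers one arm, differences between clinicians in how well or how long they treat become part of the difference between arms. Randomising youths individually does not remove this. An analysis that treats youths, or sessions, as independent leaves that variance out of the standard error. Intervals are then too narrow, and the skill of a few clinicians can be read as an effect of MATCH-ADTC.

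The plan accepts this clustering when it sizes the trial and drops it when it analyses the data. Evidence-based content is the most exposed outcome, because the unit randomised, the unit trained and the behaviour measured all belong to the clinician. The Discussion foresees core training for the workforce if results are positive, so the error rate on these tests matters.

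**Working it through.** **Inputs from the protocol article.** 60 clinicians; 400 youths, revised to 200; ICC 0.1; 15 % attrition in clinicians and clients; SD of change 4.4; difference 2; two-sided α 0.05. **Assumed:** equal caseloads unless stated, 8-20 sessions per youth, and the ICC values other than 0.1.

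**1. The plan's own figures.**
- Original detectable effect at 80 % power: (1.960 + 0.842) × √(4 × DE / N), with DE = 1 + (m − 1) × 0.1 and m = youths per clinician.
  - 60 clinicians, 400 youths: m = 6.67, DE = 1.567, effect 0.351.
  - 60 clinicians, 340 youths: m = 5.67, DE = 1.467, effect 0.368.
  - 51 clinicians, 340 youths: m = 6.67, DE = 1.567, effect 0.380.
  - No clustering: 0.280 (400 youths) or 0.304 (340 youths).

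  The stated 0.37 is reached only with the ICC.
- Revised power at 200: SE = 4.4 × √(2/100) = 0.622; 2/0.622 − 1.960 = 1.254; power 89.5 %. The stated 90 % is reproduced without any clustering. At 160 the same formula gives 82.0 %, against 80 % stated.

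**2. Brief Problem Monitor, if ICC 0.1 applies to change or slope.**
- m = 200/60 = 3.33, so DE = 1 + 2.33 × 0.1 = 1.233. The correct SE is √1.233 = 1.11 times the unclustered one.
- Type I error = 2 × [1 − Φ(1.960/1.11)] = 7.8 %.
- With attrition in both (51 clinicians, 170 youths), m is again 3.33 and the result 7.8 %. With 170 youths and 60 clinicians it is 7.2 %; with 200 and 51, 8.5 %.
- At 60 clinicians and 200 youths, other ICCs give 5.3 % (0.01), 6.4 % (0.05) and 10.6 % (0.2).
- Unequal caseloads raise it. With DE = 1 + [(1 + cv²)m − 1] × 0.1 and an assumed coefficient of variation (cv) of 0.65, DE = 1.374 and the error is 9.5 %.

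**3. Level versus slope.** The test is treatment × time. A clinician difference that shifts all of a youth's scores equally goes into the participant intercept and drops out of that contrast. A simulation with 200 youths, 60 clinicians and 16 weekly scores (the number of weeks is assumed) bears this out. With clustering in level only, type I error was 4.4 % at ICC 0.1 and 4.6 % at ICC 0.3. With a slope ICC of 0.1 and participant slopes allowed for, it was 7.4 %.

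**4. Clinician time.** There is one value per youth, so the figure of step 2 (7.8 %) holds if the ICC for minutes is 0.1. The article gives no ICC specific to this outcome.

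**5. Coded sessions.** Sessions per clinician = 0.10 × sessions per youth × 200/60.

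| Sessions per youth (assumed) | Coded per clinician | Error, ICC 0.1 | Error, ICC 0.3 |
|---|---|---|---|
| 8 | 2.67 | DE 1.167: 7.0 % | DE 1.5: 11.0 % |
| 20 | 6.67 | DE 1.567: 11.7 % | DE 2.7: 23.3 % |

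**6. Power once the clinician is included.** Effective youths per arm = 100/1.233 = 81.1; SE = 4.4 × √(2/81.1) = 0.691; 2/0.691 − 1.960 = 0.934; power 82.5 %. Keeping the unclustered power takes 200 × 1.233 ≈ 247 youths at the same caseload, hence about 247/3.33 ≈ 74 clinicians. With 60 clinicians it takes the N that solves N/(0.9 + N/600) = 200, which is 270.

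**The case against.** Four points can be made for the plan.

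- **The ICC is generic.** The article does not say whether 0.1 refers to level or change, and level clustering is harmless for treatment × time. This stands. A reader might infer that the false-positive rate must exceed 5 % on the Brief Problem Monitor; the documents do not support that without a condition.
- **The ANOVAs may be richer than they look.** The session analysis follows a US method that is not shown, the unit of analysis is not stated, and an ANOVA can include nested factors or use aggregated scores. This stands for coded sessions, where the claim has to be conditional. A reader might also infer error rates of up to about 40 %. That needs some 10 coded sessions per clinician and an ICC of 0.5, neither of which is in the article.
- **The design already limits clinician differences.** Blocking by service or team, stratifying by previous training, and model terms for service type and training can lower the residual ICC. They do not replace a clinician effect, because clinicians with the same training and service type still differ.
- **A condensed article may leave nesting to the analysis plan.** This has some force for the two ANOVAs. It has little for the Brief Problem Monitor, where the article writes out the equation, names the random effects and lists the added terms, one of them at clinician level.

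**Conclusion.** The omission is real. The plan assumes clinician clustering when it sizes the trial, and states no clinician term in any of the three primary analyses. It is firmest for the Brief Problem Monitor, whose model is written out in full.

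The size is moderate and conditional. It is about 7.8 % instead of 5 % for the Brief Problem Monitor if the ICC of 0.1 holds for change or slope, and the same for clinician time if its ICC is 0.1. For coded sessions the ranges in step 5 rest on assumed session counts and ICCs, and apply only if the cited US method does not already account for clinicians. Higher figures that rest on 40 clinicians are not supported either, since the article plans at least 60, or 51 after its own attrition allowance.

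**What to change.** - **Brief Problem Monitor:** add participant random time slopes, and a clinician random effect on intercept and time slope. The two slopes belong together, since a clinician slope without a participant slope would take up variation between youths. With about 3.3 youths per clinician the clinician slope may not be estimable, so name cluster-robust inference by clinician as the fallback.
- **Coded sessions:** use a mixed model with random effects for clinician and for participant within clinician. If the US method already does this, say so.
- **Clinician time:** use a mixed model with a random clinician effect.
- **All three:** use Kenward-Roger or Satterthwaite degrees of freedom.
- **Sample size:** restate the power at 200 as about 82.5 % at ICC 0.1, in place of 90 %.

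No new data are needed, provided each youth's and each session's clinician is recorded. The cost is wider intervals and about 7 percentage points of stated power (89.5 − 82.5). Recruitment was still open when the article was written, so the change could be made before any unblinded comparison.
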